#### Dynamic Visual Acuity

The test will measure the ability to see clearly during head rotations of greater than 100 degrees/s. A standardized Early Treatment Diabetic Retinopathy Study eye chart will be used, and the participants will be seated at a viewing distance of 4 m. Participants will be asked to read the letters on the eye chart, first with their head stationary and then when the head is passively rotated horizontally by the clinician/researcher at 2 Hz with the help of a metronome. The difference in the number of lines that participants are able to read when the head is stationary and when rotated will be used as the measure of dynamic visual acuity. A loss of 0-2 lines will be considered normal, whereas a loss of 3 or more lines will represent a loss of VOR function [37]. Moderate to high inter-rater and test-retest reliability has been demonstrated [38,39].

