### Recording and Data Analysis

The following information will be collected at baseline prior to start of the interventions: age, gender, work history, history of disease/injury process, and current medications. The assessor will be blinded to participant assignments. The primary outcome measures of the study include measurement of dynamic visual acuity, balance performance, and DHI. The secondary outcome measures of the study include gaze performance and gait analysis.

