### Statistical Analysis and Power Assessment

Descriptive statistics, including means, standard deviations, frequencies, and percentages, will be used to describe the experimental and control groups on the baseline demographic variables to achieve our first objective, which is to conduct a power analysis of the required sample size to test the difference between the experimental and controls groups at the postintervention measurement. We will test the difference between experimental and control groups on continuously and normally distributed outcome measures using analysis of covariance, with the dependent variable being the postintervention measurement of the outcome, the covariate being the preintervention measurement, and group membership being the between-participant effect. Descriptive statistics, including measures of skewness and kurtosis, will be used to assess departures from the assumptions of a normal distribution of responses. If the distribution contains extreme observations, a robust ANCOVA statistic will be adopted [49]. To test differences between experimental and control groups on discrete outcomes, such as number of times participants feel dizzy during their daily activities, we will use a Poisson regression model, with the dependent variable being the number of relevant events, the covariate being the preintervention measurement, and group membership being the between-participant effect.

To analyze the longitudinal data associated with the second objective, we will use a regression model with time as the random factor [50]. This model will be adopted because it accounts for clustering of repeated measurements within study participants and uses all available longitudinal data (ie, it does not result in case-wise deletion of study participants due to missing observations). Prior to applying this model to the data, we will conduct descriptive analyses of the proportion and pattern of missing data. To assess model fit, we will use penalized measures of the log of the likelihood function, including the Akaike Information Criterion and Bayesian-Schwarz Information Criterion. Initially we will fit a model with only a random intercept for time; subsequently, we will also consider a random slope. The intraclass correlation and the proportion of variation explained by the random effects will be calculated.

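### Dynamic visual acuity, a primary outcome, is scored in lines although participants read letters; recording letters would sharpen it at little cost

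*Protocol article*

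**What the plan says.** The Recording and Data Analysis section gives this outcome primary status: "The primary outcome measures of the study include measurement of dynamic visual acuity, balance performance, and DHI".

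The Dynamic Visual Acuity section describes the test. On the chart, "A standardized Early Treatment Diabetic Retinopathy Study eye chart will be used". On the task, "Participants will be asked to read the letters on the eye chart, first with their head stationary", and then again during passive head rotation at 2 Hz. The score is "The difference in the number of lines that participants are able to read when the head is stationary and when rotated". It is interpreted on the same scale: "A loss of 0-2 lines will be considered normal, whereas a loss of 3 or more lines will represent a loss of VOR function". On reliability the section says: "Moderate to high inter-rater and test-retest reliability has been demonstrated". It states neither the letters per line nor a rule for a partly read line, and it gives no SD for the score.

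Statistical Analysis and Power Assessment plans to compare groups on "continuously and normally distributed outcome measures using analysis of covariance", with the pre-intervention value as covariate. It adds checks of skewness and kurtosis, a robust alternative for extreme observations, and a Poisson model for discrete outcomes such as event counts. It does not name dynamic visual acuity under any of these. The sample size rests on a standardized effect of 0.80, 3 covariates explaining 10% of variance, and two-sided alpha of 0.05. This gives 46, raised to 56 for attrition.

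**The concern.** The participant reads letter by letter, but the score moves in steps of a line. It is also a difference between two such readings, so the rounding enters twice. The range that matters is short: the cut-off separates 0, 1 or 2 lines from 3 or more. On so coarse a scale, rounding noise can be a noticeable share of the between-participant variance. It affects both the post-intervention value and the baseline value used as covariate. The likely cost is some power on one of three primary outcomes in a small trial. The finer reading is available at the same test, without another measurement.

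**Working it through.** **Inputs from the article.** Effect 0.80; variance explained R² = 0.10; 3 covariates; alpha 0.05 two-sided; 46 evaluable, 1:1, so n = 23 per arm.

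**Assumptions.** 80% power (not stated in the article); 5 letters per line; a line counts as one whole unit; SD of line loss varied from 0.5 to 3 lines.

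**1. The plan's own figure.** n per arm = 2 × (1.960 + 0.842)² × (1 − 0.10) / 0.80² = 2 × 7.85 × 0.90 / 0.64 = 22.1, so 23 per arm and 46 in total. The stated 46 is reproduced at 80% power; at 85% and 90% the same formula gives 52 and 60. The noncentral t version with 3 covariates gives 48.

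**2. Power at 46 without rounding.** Degrees of freedom = 46 − 2 − 3 = 41. Noncentrality = 0.80 / √0.90 × √(23/2) = 2.86. Power = 79.7%.

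**3. Rounding variance.** A reading recorded in steps of L carries added variance of about L²/12, and a difference of two readings carries 2L²/12.
- Lines, L = 1: 2/12 = 0.167 line².
- Letters, L = 1/5 = 0.2 line: 2 × 0.04/12 = 0.0067 line².
- Reduction: 1 − 0.0067/0.167 = 96%. It does not reach zero.

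**4. Effect on power, if 0.80 is the effect on an unrounded score.** Attenuated effect = 0.80 / √(1 + added variance / SD²). For lines at SD 1, this is 0.80 / √1.167 = 0.741, with noncentrality 2.65 and power 73.4%. For lines at SD 2, it is 0.80 / √1.042 = 0.784, with noncentrality 2.80 and power 78.1%.

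| Assumed SD (lines) | Effect, line score | Power, lines | Power, letters | N for 80%, lines | N for 80%, letters |
|---|---|---|---|---|---|
| 0.5 | 0.620 | 58.0% | 78.7% | 76 | 48 |
| 1 | 0.741 | 73.4% | 79.5% | 54 | 48 |
| 1.5 | 0.772 | 76.9% | 79.6% | 50 | 48 |
| 2 | 0.784 | 78.1% | 79.7% | 50 | 48 |
| 3 | 0.793 | 79.0% | 79.7% | 48 | 48 |

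**5. Check by simulation.** ANCOVA with one baseline covariate was run 4,000 times per scenario, with readings cut down to whole units at both visits and a baseline correlation of 0.316 (squared, 0.10). At SD 1, power was 71.1% by lines, 78.6% by letters and 78.7% unrounded. At SD 2 it was 78.0%, 79.7% and 79.6%. The pattern agrees with the formula.

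**6. If 0.80 was observed on a line score.** The rounding is then already inside the effect. The line-score power is the 79.7% of step 2, and letter scoring would raise it.

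**The case against.** The strongest reply is that the line score is a documented choice. The article supports it with a cited cut-off in lines and cited reliability, and it does not show that this reliability carries over to letter counts taken during 2 Hz head rotation. That stands, and it is why the line criterion should be kept beside the letter score.

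The article also never writes that only whole lines count. It gives no credit for part of a line and its cut-off leaves nothing between 2 and 3, so whole lines is the natural reading, but it remains an inference. A full protocol may say more.

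A reader might infer that the plan treats an integer score as normally distributed. The article does not say so. ANCOVA is the likely route, since a difference in lines is not an event count, but the outcome is not assigned to it by name, and distribution checks and a robust alternative are planned.

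A reader might also infer that line scoring leaves the trial short of its planned power. The article does not support that. It states no target power, gives no SD for this outcome, and does not say which outcome the 0.80 came from.

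Finally, 36 of 56 participants (64%) were already enrolled. If their letters were not recorded, a change now would mix two scoring units in one primary outcome. That is a real cost, though a manageable one.

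**Conclusion.** The point holds as a cheap gain in precision. The stated score is coarser than the reading the test produces, on a primary outcome. Nothing in the article is contradicted by this, and line scoring is not an error.

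The size is conditional. With 5 letters per line, about 96% of the added rounding variance goes. If 0.80 refers to an unrounded scale, the gain at 46 evaluable is about 6 power points at an SD of 1 line (79.5 − 73.4), under 2 points at 2 lines, and much larger only if the SD is well below 1 line. If 0.80 was measured in lines, the sample size stands and letter scoring is a bonus.

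It would go too far to say that letters remove rounding error or cost nothing. A small rounding term remains, letters have to be written down during the test, and participants already tested may lack them.

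**What to change.** - Record the number of letters read correctly in each head condition at every remaining assessment.
- Analyse the difference in letters (head still minus head rotated) at post-intervention, adjusted for the same difference at baseline.
- Derive the line loss from the same readings and report the criterion of 0-2 against 3 or more lines alongside, for interpretation.
- For participants already tested, rescore from test sheets that show letters. Otherwise keep the line score and put it on the letter scale using the chart's letters per line. Within one visit, use the same unit for both head conditions.
- Decide and document the change before unblinding, and run a sensitivity analysis with line scores for everyone.

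The cost is a changed scoring sheet and a short note of the change, with no extra test, visit or staff. The gain is smaller to the extent that enrolled participants have only line scores.

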#### Balance Performance

The test protocol will consist of the following tasks performed in standing position for 45 seconds, first on a fixed floor surface and then repeated while standing on a compliant sponge surface, with eyes open and eyes closed, as described in Desai et al [40]. A force sensor array pressure-sensing mat (Vista Medical Ltd., Manitoba, Canada) will be used to compute the vertical center of foot pressure position in the anterior-posterior and medial-lateral directions. The total path length of center of foot pressure excursions will be computed and divided by total duration (45 seconds) to obtain average velocity. Increased center of foot pressure excursion and mean velocity has been interpreted as decreased stability [40,41]. A composite score will be computed, consisting of the 4 conditions of the modified Clinical Test of Sensory Interaction and Balance: eyes open and closed on fixed and sponge surfaces [29,36,42].

#### Dhi

The DHI has good test-retest reliability as well as face validity and internal consistency [43].

#### Gaze Performance

A computerized head-tracking task has been developed for testing gaze performance in standing position on fixed and sponge surfaces and during treadmill walking. Participants will be positioned on a treadmill 100 cm from an 80-cm monitor connected to a computer running the visual tracking application. For a full description and set up, see [name] et al [18,36]. The head-tracking task involves tracking a bright visual target that moves horizontally or vertically on a computer display in a sinusoidal fashion for several cycles. Two cursors of different colors appear on the monitor. One is the reference or target cursor, which moves at a predetermined frequency of 0.4 Hz and an amplitude of 80% of the monitor width. The second cursor is user controlled and is synced with head rotation via the head-mounted motion-sensing mouse. The task requires 60 degrees of head rotation; average velocity of 50 degree/s and peak velocity of 90 degrees/s. The goal of the visual tracking task is to overlap the 2 cursors as the target cursor moves from left to right or top to bottom of the computer display. In this task, foveation is necessary for the participant to determine the amount of overlap (error) between the moving target and head cursors, and to detect when the target cursor changes direction. The computer application also generates a logged game file to synchronously record coordinates of the target cursor and head rotation at a sampling rate of 80 Hz for offline analysis of head-tracking performance described herein. The head-tracking task will be performed for 45-60 seconds under the following conditions: (1) standing on the fixed floor surface, (2) standing on a sponge surface, and (3) during treadmill walking at a speed 0.9 m/s. Before beginning the walking plus visual-tracking test, participants will walk for 5 minutes for treadmill acclimation, and to obtain baseline data of a walk-alone condition. During testing a physical therapist will stand behind each participant, ready to provide support if needed. During the treadmill walking test, the participants will wear a safety harness secured from above to a body weight support apparatus (Biodex, model, 945-482, Biodex Medical Systems, New York, USA). Body weight will not be unloaded during testing. The sponge surface and treadmill walking tasks are included to introduce varying degrees of passive head motion [44-46]. Average angular head velocities for a fixed surface has been found to be 3 degrees/s: this increases to 8 degrees/s when standing on the sponge surface and to 30 degrees/s during treadmill walking [18]. When tested on the fixed surface with minimal passive head motion, the performance of the head-tracking task would represent the function of the smooth pursuit system and also requires VOR cancellation (ie, eyes and head moving in the same direction as the target object). When passive head motion is introduced into the visual-tracking task (especially during treadmill walking), VOR compensation is also required to maintain gaze stability [47].

The coordinate data of the computer target motion and the user head rotation (motion-sensing mouse) will be used to compute gaze performance for each head-tracking task. For a full description of the data analysis methods, see [name] et al [18,36]. A nonlinear least squares algorithm will be used to obtain a sine-wave function of the reference target cursor waveform. The first two cycles of the tracking tasks (45 seconds) will be excluded to allow participants time to acquire the moving target and begin tracking. Head rotation trajectories will be fitted to the sine-wave function, and the coefficient of determination will be computed based on the total and average residual difference between trajectories of the reference and head cursor motions. A value approaching 1 equates to perfect overlap of the two cursors, and excellent gaze performance. The coordinate data of each head-tracking trial will then be processed using custom analysis routines written in MATLAB (version 2010a; MathWorks, Natick, MA, USA).

#### Gait Analysis

A gait analysis will be conducted to examine whether the exercise program transfers to improvements in walking function. A treadmill instrumented with a pressure mat (Vista Medical, CA, USA) will be used to record vertical foot forces for each step during walking trials of 1 minute at 0.9 m/s, and thus include data for 30 consecutive steps [35,48]. The following spatiotemporal gait variables (average and coefficient of variation through 30 consecutive steps) will be computed: step and swing durations, single support times, step width, and step length.

Participants will be asked to complete daily exercise logs. The study therapist will contact each participant through phone or email on a weekly basis to obtain the exercise logs.

Interventions will begin within 1 week of the baseline assessment (primary and secondary outcome measures). The postintervention assessment will be conducted within 1 week of the final intervention session.

Participants in the experimental group will be given the visual tracking game application for home use. The game software automatically logs reference and head cursor coordinates (gaze performance) during the visual tracking task and saves the data to a coded and time-stamped computer file. Participants will be asked to play the tracking task in standing position at the beginning of every training session. This will involve 3 short tests of 45 seconds each at 3 tracking speeds. The clients can either email the data files to the investigator, or save them on a provided flash drive, which should be returned at a follow-up visit. This will allow us to perform a within individual trend analysis of up to 48 repeated measures for the experimental group.

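### The between-group gaze-performance comparison confounds task and device practice with benefit, because only the experimental arm rehearses the outcome task at home

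*Protocol article*

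**What the plan says.** Recording and Data Analysis sets the outcome tier: "The secondary outcome measures of the study include gaze performance and gait analysis". Dynamic visual acuity, balance performance and the Dizziness Handicap Inventory are primary.

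Gaze Performance describes the outcome task: "A computerized head-tracking task has been developed for testing gaze performance in standing position on fixed and sponge surfaces and during treadmill walking". On the input device it says: "The second cursor is user controlled and is synced with head rotation via the head-mounted motion-sensing mouse". The score is a coefficient of determination for head cursor against target, where values near 1 mean close overlap.

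Gait Analysis then says who takes the task home: "Participants in the experimental group will be given the visual tracking game application for home use". It sets the frequency ("Participants will be asked to play the tracking task in standing position at the beginning of every training session") and the content of each occasion ("This will involve 3 short tests of 45 seconds each at 3 tracking speeds"). It also identifies what is recorded: "The game software automatically logs reference and head cursor coordinates (gaze performance) during the visual tracking task". The stated purpose is a "within individual trend analysis of up to 48 repeated measures for the experimental group".

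Under Interventions, the control arm receives gaze stabilization exercises in clinic and a short home programme. No tracking task or head mouse is described for it. The Methods hypothesis is superiority of the home programme on gaze control, among other domains. Statistical Analysis and Power Assessment compares the arms by analysis of covariance on the post-intervention value, with the pre-intervention value as covariate. Limitations does not mention unequal exposure to the tracking task.

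**The concern.** One arm repeats the test that generates an outcome at every training session, and the other is not described as touching it between the two assessments. Skill at steering a cursor with the head improves the score whether or not gaze control has improved.

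The planned safeguards do not reach this. Baseline adjustment deals with differences present before treatment, whereas the practice comes after. Assessor blinding does not help, because practice changes the participant's own performance. Dropping the first two cycles of a trial deals with acquiring the target within that trial, not with learning over weeks. Limitations also concedes that eye movements are not recorded, so the trial's own data cannot separate a learned head-cursor skill from better gaze control.

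At stake is what a favourable group difference in gaze performance could be taken to show, given the stated hypothesis of greater improvement in gaze control.

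**Working it through.** **1. Overlap between home task and outcome task**

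- Variable: the home software logs the same reference and head cursor coordinates, and the article labels them gaze performance.
- Device: the outcome task uses the head-mounted motion-sensing mouse, which the experimental arm also uses for its games.
- Posture: the home test is done standing. The assessment covers standing on fixed floor, standing on sponge, and treadmill walking at 0.9 m/s.
- Speed: the assessment uses 0.4 Hz. The home test uses three speeds, and the article does not say whether 0.4 Hz is one of them.

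The match is closest for fixed-floor standing. Sponge is also standing, but the article does not say the home test is done on sponge. Treadmill walking is not rehearsed as a test condition.

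**2. Amount of rehearsal** (inputs from Gait Analysis: up to 48 measures; three 45-second tests per session, read as one at each speed)

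- If 48 measures means 48 sessions: 48 × 3 = 144 tests; 144 × 45 s = 6480 s = 108 minutes.
- If it means 48 single tests: 48 × 45 s = 2160 s = 36 minutes.
- Home rehearsal described for controls: none.

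The text does not settle which reading is meant, and it does not state how long the experimental home programme lasts. At five days a week, 8 weeks gives 40 sessions (120 tests, 90 minutes) and 12 weeks gives 60 (180 tests, 135 minutes). Neither equals 48. The number of measures and the programme length should be reconciled, but the point does not depend on them.

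**3. What a practice shift would do to the test** (illustration only, since the document gives no learning effect)

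First, the plan's own figure. With standardized effect 0.80, covariates explaining 10% of variance, two-sided alpha 0.05, and 80% power (assumed; the article does not state it):

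n per arm = 2 × (1.960 + 0.842)² × (1 − 0.10) / 0.80² ≈ 22.1, rounded up to 23, so 46 in total. This reproduces the stated 46.

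Now suppose the therapeutic effect on gaze performance is zero and practice alone shifts the experimental arm by b standard deviations. The noncentrality of the test is b / (√0.90 × √(2/n)), with 2n − 2 − 3 degrees of freedom. The probability of declaring a group difference is:

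| Assumed shift b (SD) | 23 per arm | 28 per arm |
|---|---|---|
| 0.1 | 6.4% | 6.7% |
| 0.2 | 10.7% | 12.1% |
| 0.3 | 18.2% | 21.3% |
| 0.5 | 41.5% | 49.0% |
| 0.8 | 79.7% | 87.2% |

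The nominal rate is 5%. An assumed shift of 0.2 to 0.5 SD would raise it to about 11% to 42% at 23 per arm.

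**The case against.** The strongest reply is that training close to the outcome is the intervention itself. The programme is deliberately task-specific: participants follow moving targets with the same head mouse for 20 minutes a day. Over 48 sessions that is 48 × 20 = 960 minutes, against at most 108 minutes of tracking tests. Device familiarity would differ by arm without any home test. This stands for the device, and no change in analysis removes it. It does not cover the tracking runs: the article calls them tests, and their stated purpose is the time-course analysis of objective 2. That rehearsal is a by-product of measurement.

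A second reply is that gaze performance is only secondary, in a pilot trial, and that dynamic visual acuity is primary and uses an eye chart with passive head rotation, with neither the application nor the mouse. This also stands, and it limits the reach of the point.

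A third is that the home and assessment set-ups differ in equipment and possibly in speed, and that the full task description is referred to other publications. This weakens the overlap, especially for sponge and treadmill, but the asymmetry remains.

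A reader might go further and infer that the comparison measures nothing but test practice, or that the trial cannot address gaze control at all. The documents support neither. No learning effect is reported, so practice is not shown to be the whole explanation of any difference, and dynamic visual acuity bears on gaze control independently of this task.

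**Conclusion.** The point holds as confounding on one secondary outcome. As planned, a between-group difference in gaze performance cannot be divided between task and device practice and therapeutic benefit. The problem is clearest for fixed-floor standing, less so for sponge and least for treadmill walking.

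The direction is expected to favour the experimental arm; the size cannot be obtained from the document. The exposure figures depend on how the 48 measures are read. The false-positive figures rest on an assumed practice shift, a zero therapeutic effect and the variance assumption of the sample-size calculation. The primary outcomes do not use this task. Objective 2 makes no group comparison, although its time course also mixes learning of the test with recovery.

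The change is worth making because it alters what the trial may conclude from gaze performance and costs little.

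**What to change.** - State that the between-group claim on gaze control rests on dynamic visual acuity.
- Use the home tracking data only for the within-arm time course of objective 2.
- Label any between-group gaze-performance result as supportive. Show treadmill walking first, as the least rehearsed condition, and do not use the two standing conditions as evidence of superior gaze control.
- Add unequal exposure to the task and the device to Limitations.

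Do not change the target frequency of the assessment. With 36 participants already enrolled, post-intervention scores at a new frequency would not be comparable with existing baselines, and the covariance analysis relies on that comparability.

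The cost is analysis and reporting wording, with no change to treatment or recruitment. One secondary outcome carries less weight in the group comparison, and device familiarity still differs by arm, so the treadmill result is only partly protected.
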